## Intervention

The intervention group will receive the “MOVEdiabetes” personalised PA consultations, pedometer (YAMAX Digi-walker SW-200) to measure weekly step counts and WhatsApp messages (Table 2).

**Table 2 Tab2:** MOVEdiabetes intervention components

Intervention visits	Weeks												
	0^a^	4	8^a^	12	16	20	24	28	32	36	40	44	48
Face to face physical activity consultations	→	↔	←										
Weekly WhatsApp step count	→	↔	↔										←
Monthly WhatsApp messages	→	↔	↔	↔	↔	↔	↔	↔	↔	↔	↔	↔	←

^a^After 7 days of PA recordings from accelerometers in the selected sub groups

### Face to face PA consultations

Recruited participants will be offered individual consultations (maximum 20 min) by the trained project officers on 3 occasions (0, 4 and 8 weeks) (Table 2). This will be undertaken a week after completing 7 days of accelerometer wear in the selected participants (accelerometer group) mostly in week 0 and 8.

The consultations aims to encourage participants towards achieving 150 min of PA per week (≥600MET-mins/week) at 12 months which has been demonstrated to be clinically effective in diabetes management. It is estimated that a step count of not less than 6000–7000 per day is required to achieve this goal [19]. Participants will be encouraged to increase their step counts gradually to achieve this goal.

PA programme design based on a theory and the behavior change techniques is widely proven to be effective [20, 21]. The theoretical framework underpinning the intervention in this study is the Health Belief Model, the Stages of Change Model and the Social Cognitive Theory [7]. The MOVEdiabetes personalised, multiple contact, intervention programme will also be based on several behavior change techniques based on the Abraham and Michie taxonomy [22] which includes (a) goal-setting for PA; (b) self-monitoring to achieve these goals; (c) frequent contact to provide accountability and sustain focus; (d) use of problem-solving to address goals and potential barriers to achieving them; and (e) emphasis on managing individual high-risk situations.

### Pedometer

Participants will be given a pedometer (YAMAX Digi-walker SW-200) at their baseline visit. Instructions on how to use the pedometer, how to record their daily steps and how to set daily step goals will be discussed by the project officers. Participants will be asked to set individual goals and fill in a daily step count to be submitted to the project officers in their respective health centres over a three month period and at 12 months.

### WhatsApp

Participants receiving the intervention will be asked to open and share a telephone WhatsApp application with the project officers in their health centre to facilitate the reporting of their step counts and get support during the intervention period. Additionally, monthly standardized physical activity motivational messages will be delivered through this telephone application. Participants are also invited to join a WhatsApp peer support group to share their experiences with other MOVEdiabetes participants.

## Process evaluation

Programme acceptability will be explored post-intervention via a brief exit questionnaire with all project officers and 50% of intervention participants randomly selected by random number tables generated in SPSSv21 by the principal investigator. The questionnaire will explore the extent initial expectations and motivations regarding the programme were met, engagement with the programme, acceptability (content, delivery and aims) of the approach e.g. if the intervention was tailored to be appropriate and realistic to the individual’s lifestyle, and elements of overall rating of the project including factors influencing willingness and ability to comply with the programme advice.

## Assessment of fidelity to protocol

Managerial:The project group will have monthly meetings to discuss issues regarding the physical activity consultations, and measurements to ensure their compliance to intervention protocol.A telephone application (WhatsApp) will be used throughout the study period by project officers and the PI to manage the daily logistics and administrative queries.Attendance sheets will be reviewed and discussed.
Qualitative:Audio-recording and transcription of 5 PA consultations randomly selected by random number tables generated in SPSSv21.Crosschecking of 10% of PA consultation notes randomly selected by a recruited external assessor.
Evaluative:The brief exit survey will include questions on adherence to the protocol specifically for project officers.

## Sample size

To demonstrate a 50% between group difference in physical activity levels (MET-mins/week) over 12 months, to be detected at a power of 80%, and significance level of 5%, 128 participants would be required to complete the study (64 in each arm). Based on a drop-out rate of 20%, 154 participants would require to be recruited (77 in each arm). Assuming a recruitment rate of 70%, 220 potential eligible participants would need to be approached.

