**Methods/design:**

The study is a one year 1:1 cluster randomized controlled trial of the MOVEdiabetes programme (intervention) versus usual care in eight primary health care centres in Oman. The MOVEdiabetes programme utilizes face to face physical activity consultations promoting 150 min of moderate to vigorous physical activity per week (≥600MET-mins/week), pedometers to self-monitor step counts and monthly telephone WhatsApp messages for follow up support. Inactive adults with type 2 diabetes and no contraindication to physical activity will be recruited over a two months period, and followed up for 12 months. To demonstrate a 50% between group difference in physical activity levels (MET-mins/week) over 12 months, (at a power of 80%, and significance level of 5%), 128 participants would be required to complete the study (64 in each arm). Based on a drop-out rate of 20%, 154 participants would require to be recruited (77 in each arm). Assuming a recruitment rate of 70%, 220 potential eligible participants would need to be approached. The primary outcome is change in levels of physical activity measured by the Global Physical Activity Questionnaire. In addition, accelerometers will be used in a sub group to objectively assess physical activity. Secondary outcomes include changes in metabolic and cardiovascular biomarkers, change in self-reported health, social support, self-efficacy for physical activity, and perceived acceptability of the program. All intervention delivery and support costs will be monitored.

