## Study design/location/recruitment

### Randomisation

The study is a 1 year 1:1 cluster randomized controlled trial of the MOVEdiabetes intervention versus usual care. A cluster randomization design was used to minimize between group contamination by having the two groups (intervention and comparison) from independent health centres. Group allocation will be generated using a random numbers table generated in SPSS v21 by an independent statistician in Oman Ministry of Health. All health centres (8) will be randomised to deliver either the intervention (*n* = 4) or usual care (*n* = 4). Health centres will be informed of their allocation verbally by the project investigator and will receive an envelope containing invitation letter and project materials.

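### The sample size matches individual randomisation although eight health centres are randomised, so 80% power and a 5% significance level cannot both hold if outcomes correlate within centres.

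*Protocol article*

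**What the plan says.** The design is clustered. The Randomisation section states: "The study is a 1 year 1:1 cluster randomized controlled trial of the MOVEdiabetes intervention versus usual care". It adds: "All health centres (8) will be randomised to deliver either the intervention (*n* = 4) or usual care (*n* = 4").

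The Sample size section targets a 50% between-group difference in MET-min/week and states that, "at a power of 80%, and significance level of 5%, 128 participants would be required to complete the study (64 in each arm"). It then allows for 20% drop-out (154 recruited, 77 per arm) and a 70% recruitment rate (220 approached). The abstract gives the same chain. Neither place states an SD, a mean, an ICC, a design effect, a cluster size or a number of clusters.

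The Statistical analysis section begins with two-sample t-tests or Mann-Whitney tests on individuals. Health centre enters a mixed model as a random effect only if differences between centres prove statistically significant.

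**The concern.** When centres are randomised, patients in the same centre share staff, setting and local habits, so their outcomes tend to correlate. Each patient then carries less independent information than in an individually randomised trial. With four centres per arm, the between-centre variance is also estimated on few degrees of freedom. A sample size that leaves this out describes a different design.

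Two errors could follow. If the analysis respects clustering, power is below the stated 80%, and a null result could be read as evidence against the programme when the trial was not well placed to detect the planned effect. If the analysis ignores clustering, most of the power survives but the false-positive rate exceeds 5%. Under the analysis as written, the second risk is the more direct one.

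**Working it through.** **Inputs from the article:** 4 centres per arm (Randomisation); 64 completers per arm, 80% power, 5% significance, 20% drop-out, 70% recruitment (Sample size). Average completers per centre: m = 64/4 = 16.

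**Assumptions, not in the article:** effect of 0.5 SD of the analysed outcome; two-sided test; ICC of 0.01, 0.02 or 0.05.

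**1. Reproducing the plan's figure.** An individually randomised t-test with d = 0.5, two-sided 5% and 80% power needs 63.77 per arm, so 64 (power 80.1%). The normal formula gives 2 × (1.960 + 0.842)² / 0.5² = 62.8, so 63. A one-sided test gives 50 and does not match. The rest of the chain is 128 × 1.2 = 153.6, so 154, and 154/0.7 = 220. No step inflates for clustering.

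**2. Power when clustering is respected.** The design effect is DE = 1 + (m − 1) × ICC. The standard error of the difference, in SD units, is √(2 × DE/64), and the noncentrality is 0.5 divided by that. The normal formula uses the critical value 1.96. The small-sample figure uses a noncentral t on 2 × (4 − 1) = 6 df, critical value 2.447.

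| ICC | DE | Effective n per arm | Noncentrality | Power, normal | Power, 6 df |
|---|---|---|---|---|---|
| 0 | 1.00 | 64.0 | 2.828 | 81% | 66% |
| 0.01 | 1.15 | 55.7 | 2.638 | 75% | 60% |
| 0.02 | 1.30 | 49.2 | 2.481 | 70% | 55% |
| 0.05 | 1.75 | 36.6 | 2.138 | 57% | 44% |

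The slack from rounding is negligible: by the normal formula, power falls below 80% once DE exceeds 64/62.8 = 1.019, an ICC of about 0.019/15 = 0.001.

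**3. Detectable effect.** On 6 df, 80% power needs a noncentrality of 3.367. Multiplying by the standard error gives 3.367 × 0.1896 = 0.64 SD at ICC 0.01, 3.367 × 0.2016 = 0.68 SD at 0.02, and 3.367 × 0.2339 = 0.79 SD at 0.05.

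**4. The unadjusted t-test planned first.** Its standard error omits DE, so its statistic has standard deviation √DE instead of 1. Type I error is 2 × Φ(−1.96/√DE). Power is about Φ((2.828 − 1.96)/√DE).

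| ICC | √DE | Type I error | Power |
|---|---|---|---|
| 0.01 | 1.072 | 6.8% | 79% |
| 0.02 | 1.140 | 8.6% | 78% |
| 0.05 | 1.323 | 13.8% | 74% |

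**The case against.** **The absence of a design effect is inferred.** The article gives no SD or formula, and a condensed article may leave an ICC to the full protocol. Other inputs come close: a difference of 0.66 SD needs 37 per arm, and 37 × 1.75 = 64.75. A reader might conclude that the sponsor certainly ignored clustering, but the article does not prove that. What stands is that the printed figures match the individually randomised calculation at a conventional effect size and show no allowance for clustering.

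**The 6 df figures belong to a test that is not planned.** This is fair. At ICC 0, the fall from about 80% to 66% comes from that choice of test alone. Hence the normal-formula figures come first here, with 6 df as the conservative bound. The planned t-test does not rescue the claim, because it keeps its power by giving up the 5% level.

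**Baseline data could recover precision.** The primary outcome is a change, and adjustment is mentioned. If 0.5 is in units of the raw SD and the baseline correlation is 0.6 at both levels (an assumption), the variance falls by the factor 1 − 0.36 = 0.64 and the noncentrality rises by 1/0.8. On 6 df, power becomes 78%, 73% and 61% at ICC 0.01, 0.02 and 0.05, still under 80%. By the optimistic normal formula it becomes 91%, 87% and 76%. So the size of the loss is not settled. However, the printed calculation claims no such gain and does not say which SD it uses.

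**The 50% label.** Without an SD or mean it is undefined; it equals 0.5 SD only if the SD equals the reference mean. A reader might go further and assume a larger SD, and so much lower power even before clustering. The article gives no SD-to-mean ratio, so no such figure is supported.

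**Conclusion.** The point holds. Eight centres are randomised, the sample size corresponds to individual randomisation at 0.5 SD, and 80% power and 5% significance cannot both hold for that effect with any ICC above a trivial value. This rests on reading the effect as 0.5 SD of the analysed outcome, which the match at 64 per arm supports but does not prove.

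The direction does not depend on the ICC chosen; the size does. Over ICC 0.01 to 0.05, power that respects clustering is 75% to 57% by the normal formula and 60% to 44% on 6 df. The planned unadjusted test has about 79% to 74% power with about 7% to 14% type I error. A reader might take 44% to 60% as the trial's actual power. The article does not support that, because it states neither an ICC nor a centre-level test.

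**What to change.** In the Sample size section and the abstract:

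- State the effect in SD units, or in MET-min/week with its SD, and say whether that SD is of the change or of the follow-up value.
- State the sponsor's own assumed ICC with a range, 16 completers per centre and 4 centres per arm.
- Replace the claim of 80% power with the power for an analysis that accounts for centre, or with the effect detectable at 80% power. On 6 df that effect is about 0.64 to 0.79 SD at ICC 0.01 to 0.05.

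In the Statistical analysis section, make that same analysis the primary one, whether or not centre differences reach significance. The restated power is valid only if the two sections agree.

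This needs no extra recruitment. The cost is a change of wording in three places, one of which changes the primary analysis, and a less favourable stated power.

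### The 20% drop-out allowance multiplies by 1.2 instead of dividing by 0.8, so 154 recruits yield about 123 completers, not the 128 required

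*Protocol article*

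**What the plan says.** The Sample size section of the protocol article sets out a three-step chain, and the Methods/design part of the Abstract repeats it with the same numbers.

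- Completers: "128 participants would be required to complete the study (64 in each arm").
- Drop-out: "Based on a drop-out rate of 20%, 154 participants would require to be recruited (77 in each arm").
- Approach: "Assuming a recruitment rate of 70%, 220 potential eligible participants would need to be approached".

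The target is described as "To demonstrate a 50% between group difference in physical activity levels (MET-mins/week) over 12 months", with 80% power at the 5% level. The section gives no standard deviation, sidedness or formula, and the article gives no other drop-out rate.

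The number 220 appears once more, in the Recruitment section that follows the exclusion criteria. There it is the number of people first offered an accelerometer, next to a 40% subset and a quota of 11 in each of the eight health centres.

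**The concern.** A drop-out rate is a proportion of the people recruited. To finish with a given number of completers, that number is divided by the proportion retained. The stated 154 looks instead like 20% added to the completers, which allows for less loss than the text says.

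If so, the plan misses its own completer target whenever its own drop-out assumption comes true, and a reader is wrongly told that 154 covers a 20% loss. Because the number to approach is built on 154, it is too low as well.

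**Working it through.** **Inputs, all from the Sample size section:** 128 completers (64 per arm), 20% drop-out, 154 recruits (77 per arm), 70% recruitment rate, 220 approached.

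**1. Reproducing the stated 154.** Completers × (1 + drop-out):
- 128 × 1.2 = 153.6, rounded to 154
- 64 × 1.2 = 76.8, rounded to 77 per arm

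Both stated figures are reproduced.

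**2. The allowance that a 20% drop-out rate requires.** Completers / (1 − drop-out):
- 128 / 0.8 = 160
- 64 / 0.8 = 80 per arm

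The stated number is 160 − 154 = 6 recruits too low.

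**3. What 154 recruits deliver.**
- 154 × 0.8 = 123.2 completers (77 × 0.8 = 61.6 per arm), about 5 short of 128
- Largest loss that still leaves 128: 1 − 128/154 = 16.9%

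**4. The next step in the chain.**
- As stated: 154 / 0.70 = 220. This step does divide by the retained proportion, so one paragraph treats its two losses in two different ways.
- Corrected: 160 / 0.70 = 228.6, rounded up to 229, which is 9 more people to approach.

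**5. Effect on power (rests on an assumption).** The protocol does not say how 64 per arm was obtained. A two-sample t-test with a standardised difference of 0.5, two-sided 5% significance and 80% power gives 63.8, rounded up to 64, so it matches. On that assumption, with patients treated as independent:

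| Completers per arm | Power |
|---|---|
| 64 | 80.1% |
| 62 | 78.9% |
| 61.6 | 78.6% |
| 61 | 78.2% |

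Steps 1 to 4 do not depend on this assumption.

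**6. The other place that uses 220.** In the Recruitment section, 8 centres × 11 = 88, and 88 / 220 = 40%. The accelerometer quota therefore agrees with 220. With 229, 40% would be 91.6, or about 11.5 per centre, and the match would be lost.

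**The case against.** The strongest reply is that the gap hardly matters. Six recruits over eight centres is 20 instead of 19.25 per centre. The assumed 20% has no stated source, 128 completers are still reached if loss stays at or below 16.9%, and the Recruitment section plans fortnightly monitoring, calls to people who miss appointments and other efforts to limit loss. All of this stands as a statement about size. None of it makes the printed figures agree with one another.

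One could also read the 20% as a simple add-on to the completers. The text calls it a drop-out rate, and the next sentence's figure comes from dividing by the retained proportion, so this reading is weak. Nor is this detail that an article leaves to a fuller document: the target, the rate and the result are all printed and do not fit together.

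Two stronger readings are tempting and go too far. A reader might infer that the plan's own power calculation falls to 78.6%. The protocol states no formula, SD or sidedness; the 0.5 SD is an inference that happens to return 64 per arm. A reader might also add the clustering question to this one, since the Randomisation section describes a trial of eight health centres. The drop-out error neither depends on clustering nor measures it. For the same reason, neither 80.1% nor 78.6% should be taken as the actual power of this cluster trial.

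**Conclusion.** The drop-out step is wrong as written, in both the Sample size section and the Abstract. Taking 128 completers and 20% loss as given, the number to recruit is 160 and the number to approach is 229, against the stated 154 and 220. The stated recruitment leaves about 123 completers, 5 below target, or covers a loss of about 17%, not 20%. This part follows from the printed figures alone.

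The consequence is small: a fall in power from about 80% to 78.2–78.9%, and only under the assumed two-sided individual-level test at 0.5 SD with clustering ignored. The error does not invalidate the trial. It deserves correction because it sits in the main sample-size statement, appears twice and sets the recruitment target.

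**What to change.** Choose one of two routes.

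1. **Keep 154 and 220.** In the Abstract and the Sample size section, state that 154 recruits give about 123 completers (about 62 per arm) at 20% loss, or 128 only if loss is at most about 17%. Do not claim that 80% power is kept at 20% loss, and do not insert a new power figure that ignores the cluster design. Cost: wording only.
2. **Keep the target of 128 completers at 20% loss.** State 160 recruited (80 per arm) and 229 approached in both places. In the Recruitment section, align the 220 and the accelerometer quota (40%, 11 per centre), and say which number the 40% refers to. Cost: 6 more recruits, fewer than one per centre, and 9 more people approached within the planned two-month recruitment period.

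Any allowance for clustering should be dealt with separately.

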## Statistical analysis

The initial quantitative analysis will be an intention-to-treat analysis between the two cluster groups (intervention versus control) but secondary analyses will explore the effect of actual treatment received. The initial analysis will involve standard two-sample comparisons (parametric or nonparametric as dictated by the distribution of the data) looking at effect sizes at 3 and 12 months using t-tests or Mann-Whitney tests for differences in means as well as repeated measures or chi squared tests for differences in proportions. Differences by health centre will be explored and, if statistically significant will be entered in a mixed model as a random effect. The balance of characteristics between treatment and control arms will be tabulated and if differences are noted, adjustment will be made for these in linear regression models.

Results from the open-ended questions in the exit survey will be analysed thematically to identify the perceived acceptability of the intervention (content, delivery and aims) to the participants and project officers (health care providers).

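### Clustering by health centre is modelled only if a significance test detects it, so the between-arm tests exceed their nominal 5% false-positive rate

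*Protocol article*

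**What the plan says.** The Randomisation section makes the health centre the unit of allocation: "The study is a 1 year 1:1 cluster randomized controlled trial of the MOVEdiabetes intervention versus usual care". All eight centres are allocated, four to each arm. The reason given is "A cluster randomization design was used to minimize between group contamination".

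The Statistical analysis section then sets the intention-to-treat comparison at participant level: "The initial analysis will involve standard two-sample comparisons (parametric or nonparametric as dictated by the distribution of the data"). For the follow-ups at months 3 and 12 it names these tests: "using t-tests or Mann-Whitney tests for differences in means as well as repeated measures or chi squared tests for differences in proportions". None of these tests, as named, has a term for centre. Centre enters by one route only: "Differences by health centre will be explored and, if statistically significant will be entered in a mixed model as a random effect". No other section makes allowance for clustering unconditional, and the Sample size section mentions neither an ICC nor a design effect.

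**The concern.** Participants of one centre share staff, catchment area and routine care. Under the Recruitment section, the centre's own project officers also screen them, record their outcomes and, in the intervention arm, deliver the programme. Some correlation within centres is therefore likely. When it exists, a participant-level test uses too small a standard error for the arm difference.

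The plan treats this as a matter for the data to settle. That is unsound: the design fixes the error term, and a non-significant centre test with four centres per arm does not show that clustering is absent. Most of the time at small to moderate ICC, the test will miss the clustering and the unadjusted analysis will stand. A significant result could then reflect nothing more than which centres fell into which arm. The Conclusion section says the results are meant to inform Ministry of Health policy and practice, so a false positive would have consequences.

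**Working it through.** **Inputs.** Eight centres, four per arm (Randomisation); 128 completers, 64 per arm, 80% power, 5% significance (Sample size). Assumptions, because the protocol does not give them: two-sided testing, equal centres of 128/8 = 16, normally distributed outcome with total variance 1, ICC from 0 to 0.10.

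**The plan's own figure.** The target is "To demonstrate a 50% between group difference in physical activity levels (MET-mins/week) over 12 months", with no standard deviation. Read as a standardised difference of 0.5, the normal formula gives 2 × (1.96 + 0.84)² / 0.5² ≈ 63 per arm, and the two-sided t-test version gives 63.77, so 64. The stated 64 per arm is thus reproduced as an individually randomised calculation; one-sided testing would give 51.

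**Unadjusted test, by formula.** Design effect DE = 1 + (16 − 1) × ICC. Actual two-sided error = 2 × [1 − Φ(1.96/√DE)]. At ICC 0.05: DE = 1.75, 1.96/1.323 = 1.48, error = 13.8%.

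**Whole rule, by simulation.** 20,000 null trials per ICC (Monte Carlo standard error about 0.15 percentage points near 5%). Step 1 is an F-test for centre at 5%. If it is significant, a random-centre analysis follows; if not, the participant-level t-test is kept. The protocol does not say whether the centre test is done within arms or across all eight centres, nor whether the mixed model would use a t reference on 6 degrees of freedom or a normal (z) reference, so all four variants were run. Results in %:

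| ICC | DE | t-test, formula | t-test, simulated | Mann-Whitney | Centre test significant: within arms / all 8 | Rule, within arms: 6 df / z | Rule, all 8: 6 df / z | Centre always included, 6 df |
|---|---|---|---|---|---|---|---|---|
| 0 | 1.00 | 5.0 | 4.8 | 4.8 | 5.0 / 4.9 | 4.6 / 4.6 | 4.0 / 4.2 | 4.9 |
| 0.01 | 1.15 | 6.8 | 6.7 | 6.6 | 9.1 / 9.1 | 6.1 / 6.1 | 5.1 / 5.6 | 5.2 |
| 0.02 | 1.30 | 8.6 | 8.5 | 8.3 | 13.6 / 14.5 | 7.4 / 7.5 | 5.8 / 6.5 | 4.9 |
| 0.05 | 1.75 | 13.8 | 13.9 | 13.4 | 31.7 / 34.1 | 9.6 / 10.0 | 6.6 / 8.3 | 4.9 |
| 0.10 | 2.50 | 21.5 | 21.9 | 21.1 | 57.7 / 62.2 | 10.3 / 11.8 | 6.7 / 9.7 | 5.0 |

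With the within-arm test, the unadjusted analysis is kept in about 86%, 68% and 42% of trials at ICC 0.02, 0.05 and 0.10. Among those trials, its error rate is 8.6%, 14.0% and 22.9%, no better than with no screening at all. The overall rate falls only because the other trials switch to the centre-level test.

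**Power once centre is always included.** Non-centrality = 0.5/√(2 × DE/64), referred to a t distribution on 6 df at two-sided 5%. At ICC 0.05 this is 0.5/0.234 = 2.14, giving 44%. The results are 66%, 60%, 55%, 44% and 33% at ICC 0, 0.01, 0.02, 0.05 and 0.10.

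**The case against.** Several counter-arguments have some force.

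- **The plain t-test is not the whole plan.** True: the protocol goes on to look at centre differences. The rates for the conditional rule are the fair measure of what is written, and they are lower. They still exceed 5% in every variant from ICC 0.02 upwards.
- **A centre test across all eight centres does less harm.** Also true. Followed by a 6-df test, it gives 5.1% at ICC 0.01 and 6.7% at 0.10. A real treatment effect can trigger this version of the test, but that moves the trial to the clustered model, so it adds no false positives. It does make the choice of model depend on the effect under test, and the protocol does not say which version applies.
- **The ICC is unknown, and at zero there is no inflation.** Correct, but nothing in the protocol supports an ICC of zero. Likewise, the unadjusted test is not usually kept at every ICC: at 0.10 the centre test is significant in more than half of trials.
- **The text calls this the initial analysis, and a fuller plan may exist.** No other intention-to-treat comparison between arms is specified except through the condition or through covariate adjustment. The conditional rule is stated outright, so the objection is to a rule and not to missing detail.
- **The remedy is more than a change of wording.** This stands: the fall in power bears on the Sample size section and should be stated openly.

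**Conclusion.** The rule is wrong as written. Centres are the randomised units, so allowance for centre cannot depend on a significance test. With eight equal centres of 16 and an assumed ICC of 0.02 to 0.10, the stated procedure has a false-positive rate between 5.8% and 11.8% at a nominal 5%. The participant-level tests alone run from about 8% to 22%. At ICC 0.01 the rule gives 5.1% to 6.1%, and at ICC 0 there is no inflation. The exact size depends on the true ICC, on the centre sizes and on the unspecified details of the two steps. A centre-level analysis on 6 df holds 4.9% to 5.2% throughout.

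**What to change.** Delete the condition on statistical significance. Make the primary comparison a linear mixed model with a random intercept for health centre, included whatever its estimated size, with small-sample degrees of freedom (Kenward-Roger or Satterthwaite). State that the between-centre degrees of freedom are kept even if the centre variance is estimated as zero; otherwise the model can fall back to the participant-level test. A t-test on centre means with 8 − 2 = 6 df is a simple alternative. The two agree exactly only with equal centre sizes and no individual covariates, so one should be named as primary.

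Replace the participant-level Mann-Whitney and chi-squared tests with cluster-level counterparts: transformed MET-min/week, centre-level proportions, or a permutation test over the 70 possible four-four allocations (smallest two-sided p-value 2/70 = 0.029).

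The change needs new analysis text and a little more programming, and no further data. Confidence intervals will be wider. The power figures above also mean that the Sample size section should be restated with an assumed ICC and the eight-centre limit. That loss comes from the design; the present rule only hides it.
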